### Implementation {16c}

Randomization is carried out by a staff member outside the research group who generates the allocation sequence and assigns participants to interventions.

## Blinding

### Who will be blinded {17a}

Participants, care provider, investigator, and outcomes assessor are blind to the information about group allocation.

### Procedure for unblinding if needed {17b}

The participants are instructed in advance not to reveal allocation to researchers in any evaluation. We do not anticipate any requirement for unblinding but if required, the trial manager and data coordinator will have access to group allocations and any unblinding will be reported. Principal investigator (PI, YC) will feed data into the computer.

## Data collection methods

### Plans for assessment and collection of outcomes {18a}

#### Primary study parameter/endpoint

##### BSI

The primary outcome criterion is the reductive ratio in BSI score after 1 and 2 weeks of the treatment. A treatment response is defined as a 50% reduction in the BSI score and remission is defined as score of 6 in the BSI at any point during the 8-week trial compared with the baseline.

Secondary study parametersMini-International Neuropsychiatric Interview (MINI);HAMD-17, MADRS, and ODQ;YMRS;CGI;SDS;WCST and SCWT;Peripheral venous blood: Biomarkers representing inflammatory mechanisms associated with suicidal ideation and MDD are assessed. (1) Routine tests: The routine tests include calculation of the WBC, CRP, neutrophils, lymphocytes, monocytes, platelets. (2) Specific tests: We collect the peripheral blood serum and store it at −80°C after centrifugation. We examine the NGF, BDNF, GDNF, IL, TNF-α, sTNFr1, sTNFr2. NLR, MLR, and PLR in serum using ELISA.

Data collection will be performed by staff of study who will be trained in how to do assessments. Participants will be familiarized with the equipment and tests of study during screening. For all participants, data collection will be conducted at a certain time, in face-to-face meetings. The peripheral blood collection will be done at the laboratory in Shanghai Mental Health Center.

Participants will receive a SMS text or an email to remind their appointment the day before. PI (YC) of the study will supervise data collection to check the quality, completeness, plausibility, and possible errors of the collected data.

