**Fig. 1 Fig1:**
[figure not shown]
Trial flowchart. We plan to recruit 76 patients with MDD. For the patients who take no psychotropic drug at baseline or maintain actual pharmacotherapy for at least 2 weeks before the stimulation initiation and during the whole stimulation period. The patients will be randomized (1:1) into one of the following two groups: tDCS group or sham group. Primary and secondary study parameters will be accessed at baseline (week 0), the 1st week (after 5 sessions), 2nd week (after 10 sessions), 4th week (2 weeks after intervention), 6th week (4 weeks after intervention), and 8th week (6 weeks after intervention)

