### Eligibility criteria {10}

#### Inclusion criteria

Ages are from 18 to 50;Meeting the criteria of the Diagnostic and Statistical Manual of Mental Disorder (DSM-5) for current unipolar MDD, which is assessed by at least one professional psychiatrist;Han ethnicity;Right handedness;With a score≥17 on the HAMD-17 [16];With a score≥6 on the BSI [17];Without any pharmacotherapy at baseline or maintaining actual pharmacotherapy for at least 2 weeks before the stimulation initiation and during the total stimulation period.

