### Intervention description {11a}

Participants will receive one of two interventions: tDCS group or sham group. For brain stimulation, tDCS-CT devices (Neuroelectrics, Starstim 8, USA) are used. The stimulation protocol A or B will be administered in a software matched by tDCS device and by a staff member outside the research group with password. The research group cannot obtain the password during the trial. The participants will receive tDCS stimulation of protocol A or B as randomized from start to finish. The anode and cathode electrodes are inserted in saline-soaked sponges with diameter of 3.2cm and then positioned over the left and right dorsolateral prefrontal cortex (DLPFC) using specific headgear [19]. Each session uses a 2mA current and lasts 60 min. Ten sessions are daily performed on weekday. For sham, the current rapidly ramp up to 2mA over the first 30s and rapidly ramped down to 0mA over the next 30s automatically to allow participants to feel typical initial sensations of active tDCS [20, 21]. Trained psychiatrists and psychologists blind to group assignment administered the tDCS regimen. After completing ten sessions, no treatment is interdictory.

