### Criteria for discontinuing or modifying allocated interventions {11b}

If participants do not meet the inclusion criteria;If participants or their guardians decide to leave the study;If participants develop a serious physical disease whether or not it is related to tDCS;If participants stop taking their medication for three consecutive days, stop effective contraception or become pregnant;If participants use other treatments (including MECT, rTMS);If other conditions occur, and the investigator decides to terminate the study;Defaulting.

During 10 sessions, modification of dose is not permitted. When ceasing treatment, no treatment is interdictory and participants could follow psychiatric routine.

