### Provisions for post-trial care {30}

No provisions for post-trial care are planned. Patients could follow psychiatric routine after the completion of 10 sessions.

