### Outcomes {12}

#### Primary outcome

The primary outcome is defined as reductive ratio of BSI after 1 and 2 weeks, as well as, after 5 and 10 sessions.

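### Remission is set at the score that also qualifies a patient for entry (BSI 6) and counts at any point in 8 weeks, so it needs no improvement from a patient entering at 6 and does not isolate the stimulation course

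*Protocol article*

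**What the plan says.** All references are to the protocol article.

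- **Remission** (Plans for assessment and collection of outcomes {18a}, BSI): "remission is defined as score of 6 in the BSI at any point during the 8-week trial compared with the baseline". No inequality, minimum fall, fixed visit or sustained score is given.
- **Response** (same place): "A treatment response is defined as a 50% reduction in the BSI score", also without an inequality.
- **Entry** (Inclusion criteria): "With a score≥6 on the BSI".
- **Primary outcome** (Outcomes {12}): "The primary outcome is defined as reductive ratio of BSI after 1 and 2 weeks".
- **Visits** (Fig. 1 legend): after baseline, weeks 1 and 2 (after 5 and 10 sessions), then the "4th week (2 weeks after intervention), 6th week (4 weeks after intervention), and 8th week (6 weeks after intervention").
- **Treatment after the course**: "After completing ten sessions, no treatment is interdictory" (Intervention description {11a}); "Patients could follow psychiatric routine after the completion of 10 sessions" (Provisions for post-trial care {30}). The same holds after early cessation: "When ceasing treatment, no treatment is interdictory and participants could follow psychiatric routine" (Criteria for discontinuing or modifying allocated interventions {11b}). Section {18b} keeps collecting outcomes from patients who discontinue.
- **Use**: Statistical methods {20a} lists response and remission rates among the comparisons between groups. They stand, oddly, inside a sentence on baseline variables, but neither rate can be a baseline quantity.

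**The concern.** Remission should mark a state the patient was not in at entry. Here the entry range and the remission score share the value 6, so the definition can be met without change. The window also runs four times as long as the two-week stimulation course. A patient can be credited with remission on the strength of one visit in week 4, 6 or 8, after starting some other treatment, including MECT or rTMS, whose use during the trial is a reason for discontinuation under {11b}.

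At stake is a between-group remission rate that readers will be inclined to quote. As defined, its level is raised by repeated looks and possibly by non-trial treatment, and the contrast between arms is not a contrast of the stimulation course alone. The protocol has fixed this rule, so it is not a detail left to an analysis plan.

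**Working it through.** The protocol gives no remission rate, so there is no figure to reproduce. The check is logical, with two illustrations.

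**1. Overlap of entry and remission.** Entry is BSI ≥ 6. Three readings of the remission score:

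| Reading | Enters at 6, still at 6 | Falls to 5 or lower |
|---|---|---|
| exactly 6 (literal) | remitter, no change | not a remitter at that visit |
| ≤ 6 | remitter, no change | remitter |
| < 6 | not a remitter | remitter |

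Only the third removes the overlap. An inequality may have been lost from the text, although the sign in the inclusion criterion survives.

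**2. Window.** Post-baseline visits are weeks 1, 2, 4, 6 and 8. Stimulation ends at week 2. So 3 of 5 visits, and 8 − 2 = 6 of 8 weeks, follow the last session.

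**3. Cumulative against single-visit rate.** P(at least one of five visits) ≥ P(any one of them). This needs no assumption. For its possible size, assume the same rate p at each of five visits, governed by equally correlated normal variables with correlation r:

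any-visit rate = 1 − ∫ φ(z) · Φ((c − √r·z)/√(1 − r))⁵ dz, with c = Φ⁻¹(1 − p).

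| r | p = 20% | p = 30% | Difference (points) | Odds ratio | Risk ratio |
|---|---|---|---|---|---|
| single visit | 20% | 30% | 10 | 1.71 | 1.50 |
| 0.8 | 37% | 50% | 13 | 1.71 | 1.36 |
| 0.7 | 41% | 55% | 14 | 1.74 | 1.34 |
| 0.5 | 49% | 63% | 15 | 1.82 | 1.30 |

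Both levels rise. If 20% and 30% are taken as the two arms, the risk difference widens, the odds ratio does not fall, and only the risk ratio shrinks.

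**4. Patients with no true change.** Assume independent visit-to-visit noise with SD 2 to 4 BSI points and scores rounded to whole numbers (simulated, 200,000 patients per setting):

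| Baseline | Reading | Week 2 only | Any of five visits |
|---|---|---|---|
| 6 | ≤ 6 | 55–60% | 98–99% |
| 6 | exactly 6 | 10–20% | 41–67% |
| 8 | ≤ 6 | 23–35% | 72–89% |
| 8 | < 6 | 11–27% | 43–79% |

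Reading the cut-off as < 6 removes the entry overlap but not the inflation from the window. The noise SD is an assumption, as the protocol gives none, and independence between visits makes the any-visit column high. The table shows the mechanism and does not forecast this trial.

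**The case against.** **Remission is a supporting measure.** It is neither the primary outcome nor named among the secondary outcomes in {12}, and the acute objective is carried by the BSI reductive ratio at weeks 1 and 2. This stands and limits the weight of the point. It does not remove it, because {20a} compares the rates between groups.

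**Patients as remitters at baseline.** A reader might infer that someone entering at 6 is already in remission at entry. The definition speaks of the trial period compared with baseline, which points to post-baseline visits. The supportable statement is narrower: such a patient counts if still at 6 later.

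**Dilution of the arm difference.** A reader might infer that repeated chances shrink the treatment contrast. The table in step 3 does not show that: the risk difference grows from 10 to 13–15 points. Unrestricted later treatment, or an effect that fades after week 2, could dilute the contrast or distort it either way. The documents do not allow either to be sized.

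**Remission easier than response.** From a baseline of 6 to 11, reaching 6 needs less than a 50% fall, for example (8 − 6)/8 = 25%. It is tempting to call this an error of the plan. Any fixed cut-off near the entry threshold does the same: with BSI below 6, baselines 6 to 9 still remit on less than 50%, for example (8 − 5)/8 = 37.5%. It is not a ground for this point.

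**Scope of the any-point phrase.** It clearly attaches to remission but may not govern response, and it could mean that the criterion is applicable at whichever visit is examined. {20a} does not say the rates are cumulative. This is a fair ambiguity, and one more reason to name the visit.

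**Later visits have a purpose.** The Discussion wants them for the course and persistence of effects, and {13} schedules medication use inventories. Both fit descriptive reporting by visit and do not call for a cumulative rate.

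**Conclusion.** The point holds for the remission definition. As written, or read as 6 or below, remission can be met with no improvement by a patient who enters at 6; read literally, it also excludes better scores. Taken as cumulative, the rate is at least as high as at any single visit, and 3 of the 5 visits it draws on follow the end of stimulation, when no treatment is barred. The between-group remission comparison therefore does not isolate the effect of the stimulation course.

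The size in this trial is unknown. The number entering at exactly 6 is not given, nor are visit rates, correlations or score variability. The illustration of 20% becoming 37% to 49% rests on an assumed constant per-visit rate and correlations of 0.8 to 0.5. The direction of any distortion of the arm difference is uncertain. The primary outcome is unaffected, so this should be corrected but does not threaten the main result.

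**What to change.** In {18a}, define response as a reduction of at least 50% from baseline in BSI, and remission as BSI below 6, that is, below the entry threshold. Assess both at the two primary time points, week 1 and week 2, each reported separately. Replace the any-point clause with a statement that weeks 4, 6 and 8 are reported by visit, descriptively, alongside the other treatments received by then. In {20a}, move the response and remission comparison out of the sentence on baseline variables and name the visits to which it refers.

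The cost is wording only, since the BSI scores are already planned at these visits. Reported remission rates will be lower than under an any-visit reading of 6 or below. The Trial status section describes the trial as still enrolling, and {16b} keeps allocation concealed until the analyses are complete. If the change is made before any comparison by arm has been seen, it can be documented as an amendment through the route in {25}.

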### Plans to promote participant retention and complete follow-up {18b}

Combined with a pragmatic approach, and an emphasis on the importance of participating in research, this hopefully keeps enrolled participants in the study and makes them complete follow-up interviews. Outcome data will also be collected for participants who discontinue or deviate from intervention protocols.

### Participant timeline {13}

All the time points for the physical examinations, scale assessments, medication use inventories and laboratory examinations are shown in Table 1.

**Table 1 Tab1:**
[figure not shown]
Data collection methods and clinical assessment time points

**−*****t***_***1***_: 2 weeks before allocation; ***t***_***1***_: the 1st week (after 5 sessions); ***t***_***2***_: the 2nd week (after 10 sessions); ***t***_***3***_: the 4th week (2 weeks after intervention); ***t***_***4***_: the 6th week (4 weeks after intervention); ***t***_***5***_: the 8th week (6 weeks after intervention)

### Data management {19}

At the beginning of the study, participants will be assigned a unique identification code and the data sent to the study assessor will only include the code without participant identification information. Subjective assessments and demographic information collected on paper forms first and then will be entered into specific SPSS files by PI. And a second study staff member will check the data entry process for accuracy. All paper-based data for the study including consent forms, identifiable information, objective questionnaires, and subjective assessments will be kept separate from each other in a locked cabinet in the PI’s office of Shanghai Mental Health Center. The electronic records of the study, i.e., raw data of biomarkers, and the SPSS files stored on a password-protected external hard drive and computer. Both paper and digital documents will only be accessible to the research team. All of the data management work will be done at Shanghai Mental Health Center. A complete back-up of the primary database will be performed twice a month via netdisk with password.

### Composition of the data monitoring committee, its role and reporting structure {21a}

A Data Monitoring Committee (DMC) has been established in the hospital to monitor study conduct, the safety, efficacy. The DMC is composed of clinicians independent of the study and statistician and independent from the sponsor and competing interests.

### Interim analyses {21b}

We perform an interim analysis on the primary endpoint when 30 and 70% of patients have been randomized and have completed the 8-week follow-up. The interim analysis is performed by an independent statistician. The statistician will report independently to the DMC. The research team will have access to these interim results and the DMC could make the final decision to continue or terminate the trial.

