### Sample size {14}

The sample size was calculated based on the data from Kalu et al. [22] and Boggio et al. [23]. In these studies, the active tDCS was assumed to be superior to sham tDCS in controlling depression with a conservative mean diference of 0.74 and standard deviation (SD)=25.8. We set the type 1 error, *α* (significance), and the a power at 80%. We used G power software (V.3.1.9.4) to calculate the sample size. The result indicated that a minimum of 30 patients per group are needed (a total of 60 patients). Considering the 20% drop-out rate, 75 patients are needed in our experiment. Finally, we planned to enrol 38 patients per group for a total of 76 included patients.

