## Statistical methods

### Statistical methods for primary and secondary outcomes {20a}

Descriptive analysis will consist of means and SD for continuous variables and percentages for categorical variables. Data normality will be tested with the results expressed as mean ± SD or percentage, whenever appropriate. Non-parametric tests will be used if data were not normally distributed. Baseline variables will be compared between the groups using either the Student *t* test or chi-squared test (e.g., sociodemographic data, cognitive function data, biomarkers representing inflammatory mechanisms associated with suicidal ideation and MDD, response and remission rates between groups). To compare primary endpoint, a two-way ANOVA will be used considering group (intervention and sham-control groups) and time points (pre and post-intervention), followed by the Bonferroni post hoc test, in case of significant F ratios. Using a mixed-effects model for repeated measures to analyze change from baseline of BSI scores, time, and their interaction. We will also adopt pretreatment values (e.g., age, gender, baseline BSI, HAMD-17, CRP, and blood cells level) as covariates to correct the possible differences. An intention-to-treat analysis will be conducted, i.e., all participants, regardless of adherence to the intervention, will be included in the final analysis. All calculations will be performed using the R-softawre, and the significance level will be set at *P* ≤ 0.05.

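### Two interim analyses of the primary endpoint, with power to terminate, stand beside a single level of P ≤ 0.05 and no boundary; if that level serves at every look, the type I error is about 10.8%

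*Protocol article*

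**What the plan says.** Section {21b} of the protocol article plans the looks as follows: "We perform an interim analysis on the primary endpoint when 30 and 70% of patients have been randomized and have completed the 8-week follow-up". After these looks, "the DMC could make the final decision to continue or terminate the trial". No test, threshold or stopping direction is given.

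The DMC section {21a} says that the committee was set up "to monitor study conduct, the safety, efficacy".

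Statistical methods {20a} gives the only significance level in the article: "the significance level will be set at *P* ≤ 0.05". It is tied to all calculations and names no exception for interim or final tests. The Bonferroni step in that section is a post hoc test after a significant F ratio. It does not address repeated looks over time.

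Sample size {14} gives no number for alpha: "We set the type 1 error, *α* (significance), and the a power at 80" per cent. It mentions no allowance for interim analyses.

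**The concern.** Testing the same endpoint three times as data accumulate gives a null effect three chances to cross the line. Unless the looks share one 5% budget, the false-positive rate of the primary claim exceeds 5%. Here the article fixes the look times, the endpoint, the power to terminate and one level of 0.05, but not how these fit together. A full SAP could add interim boundaries. However, a rule that allows an efficacy stop at the interims and holds exactly 5% overall needs a final level below 0.05, which would then disagree with {20a}.

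An efficacy stop at the first look would also rest on about 11 or 12 patients per arm. At that size only a large observed effect reaches significance, so the reported benefit on suicidal ideation would tend to be exaggerated.

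**Working it through.** **Inputs.** Planned total 76, allocated 1:1, with looks at 30% and 70% ({14}, {8}, {21b}). 0.30 × 76 = 22.8 and 0.70 × 76 = 53.2, so about 23 and 53 patients. The level is 0.05 ({20a}), taken as two-sided because the article does not say. Information is taken as proportional to patients: t = 0.3, 0.7, 1.0.

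**The plan's own figure.** Section {14} quotes "a conservative mean diference of 0.74 and standard deviation (SD)=25.8". A single-look two-sample t test with standardized difference 0.74, two-sided 0.05 and 80% power needs 29.66, so 30 per group. Then 60 / 0.80 = 75, which the plan raises to 76. The stated size is reproduced by a fixed design with one analysis at 0.05. (Read literally, 0.74 with SD 25.8 would need 19,082 per group; that is a separate matter.)

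**Type I error if 0.05 is used at each look.** Under the null, the three Z statistics are jointly normal with corr(Z_i, Z_j) = √(t_i/t_j) for t_i < t_j:

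- corr(Z₁, Z₂) = √(0.3/0.7) = 0.655
- corr(Z₁, Z₃) = √0.3 = 0.548
- corr(Z₂, Z₃) = √0.7 = 0.837

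The overall error is 1 − P(|Z₁|, |Z₂|, |Z₃| all ≤ 1.96). The cumulative values are:

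| After look | Overall error |
|---|---|
| 30% | 0.050 |
| 70% | 0.085 |
| Final | 0.108 |

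Simulation of the Z process gives 0.108, and so does a t-test simulation with 11, 27 and 38 per arm. The ratio is 0.108 / 0.05 = 2.2. Three independent tests would give 1 − 0.95³ = 0.143, which is too high here because the looks share data.

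**If the interim bounds were strict and the final test stayed at 0.05.**

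- p < 0.001 at both interims: overall 0.0505.
- O'Brien-Fleming bounds at the interims: overall 0.055.

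**Levels that hold 5% overall (nominal two-sided p).**

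| Rule | 30% | 70% | Final |
|---|---|---|---|
| Lan-DeMets O'Brien-Fleming-type | 0.00035 | 0.0190 | 0.0430 |
| O'Brien-Fleming | 0.00025 | 0.0164 | 0.0446 |
| Pocock | 0.0218 | 0.0218 | 0.0218 |

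The first row uses the spending function α(t) = 2 − 2Φ(1.96/√t), with Z bounds 3.578, 2.345 and 2.024. In each row the final level is below 0.05.

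**Cost.** With the Lan-DeMets bounds, a design with 80.0% fixed-sample power keeps about 79%. Restoring 80% under O'Brien-Fleming multiplies the size by 1.018: 60 × 1.018 = 61.1 evaluable, and 61.1 / 0.80 = 76.4, so about 77 enrolled.

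**First look.** Significance at 0.05 needs an observed standardized difference of t(0.975, df) × √(1/n₁ + 1/n₂). This is 0.89 with 11 per arm and 0.85 with 12 per arm, against a planning value of 0.74.

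**The case against.** The strongest reply is that {21b} states no threshold. A reader might infer that 0.05 at all three looks is a rule of the plan. It is not written there: the level comes from {20a}, which does not mention the interim looks. Nor is the stopping direction stated. Termination could be for harm or futility, and looks of that kind with no efficacy stop do not raise the type I error. Boundaries are often placed in an SAP or DMC charter, neither of which is shown, and with very strict interim bounds a final 0.05 leaves the error at 5.1% to 5.5%. All of this stands, and it makes the 10.8% conditional.

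It does not remove the point. The looks are on the primary endpoint, efficacy is in the DMC's remit, termination is allowed, and one level is fixed for all calculations with no reference to another document for a different one. An unseen boundary that spends alpha and holds exactly 5% would contradict {20a} as printed.

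A reader might also be tempted to raise the figure further because the primary outcome is read after both 5 and 10 sessions. The article does not support a number for that: it gives no correlation between the time points, and {20a} describes a Bonferroni step after the ANOVA. That is a separate question.

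The missing sample-size allowance carries little weight, since O'Brien-Fleming-type bounds need about one more patient.

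**Conclusion.** The concern holds in conditional form. The article plans two analyses of the primary endpoint with power to terminate, and gives one significance level that is not reconciled with them. If that level is applied at each look and an efficacy stop is allowed, the overall two-sided type I error is about 10.8%, or 2.2 times nominal. Strict interim bounds with a final 0.05 would reduce the excess to between 0.05 and 0.5 percentage points, and looks without an efficacy stop would produce none. The figures assume two-sided tests and information proportional to patients. Because the choice among these readings decides whether the primary claim has a 5% error rate, it should be settled before any look informs a decision to continue.

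**What to change.** State the purpose of the looks in {21b} and make {20a} agree. Either:

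- (a) Name a Lan-DeMets O'Brien-Fleming-type spending function, with nominal two-sided p of about 0.0003 at 30%, 0.019 at 70% and 0.043 at the final analysis, and replace the final level in {20a} accordingly. The bounds should be recomputed from the actual information if the looks fall at other fractions. The cost is about 1 percentage point of power (80.0% to about 79%) at the same enrolment.
- (b) Declare both looks non-binding safety or futility looks with no efficacy stop, and keep 0.05 for the final test. This costs no alpha.

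Either way it is one paragraph in the protocol, repeated in the DMC charter.

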### Concealment mechanism {16b}

Personnel who are not blind to the treatment arm are responsible for the randomization process where REDCap is used. When a participant has been recruited for the study and baseline assessment has been conducted, the person responsible informs the assessor the result of randomization, group A or B, process via email. The actual intervention will be unknown to the researchers and clinicians. The randomized intervention allocation is concealed until the statistical analyses of the resulting data have been completed and conclusions have been drawn.

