### Confidentiality {27}

All study-related information and participant information will be stored in locked file cabinets in areas with limited access. All laboratory specimens and data reports will be accessed by a coded ID number. All records that contain names or other personal identifiers will be stored separately from study records. All local databases will be accessed by password. PI will be given access to the cleaned data sets. All data will be password protected. To ensure confidentiality, project team members will be blinded to the data.

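### The protocol gives the research team unrestricted access to interim primary-endpoint results during the trial, which conflicts with {27} and weakens the blinding set out in {11a}, {16b} and {17a}

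*Protocol article*

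**What the plan says.** Interim analyses {21b} fixes the looks: "We perform an interim analysis on the primary endpoint when 30 and 70% of patients have been randomized and have completed the 8-week follow-up". An independent statistician carries them out, and "The statistician will report independently to the DMC". The closing sentence of the section begins: "The research team will have access to these interim results". It goes on to leave the final choice between continuing and stopping to the DMC.

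Other sections bear on who may know what:

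- **Confidentiality {27}:** "To ensure confidentiality, project team members will be blinded to the data".
- **Concealment mechanism {16b}:** "The randomized intervention allocation is concealed until the statistical analyses of the resulting data have been completed and conclusions have been drawn". The same section says that, after baseline assessment, "the person responsible informs the assessor the result of randomization, group A or B, process via email".
- **Who will be blinded {17a}:** "Participants, care provider, investigator, and outcomes assessor are blind to the information about group allocation".
- **Intervention description {11a}:** the password that separates stimulation protocols A and B is withheld from the research group for the duration of the trial.
- **Responsibilities of TSC:** the research coordinators run the device, gather the data and see the patients at follow-up. Recruitment {15} describes the enrolment group, which includes students and psychiatrists.
- **Sequence generation {16a}:** clinician scales are given by trained, blinded study staff.

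**The concern.** An independent interim statistician and a DMC exist so that people who can influence the remaining data do not learn how the comparison is going. The last sentence of {21b} undoes that arrangement straight after setting it up. No section limits the team's access to pooled data or to the DMC's recommendation, and none limits it to staff who have no part in treatment or assessment.

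The primary outcome is change in a suicidal-ideation scale, which is open to expectation. Knowledge of an interim trend can alter how patients are approached, what they are led to expect and how later assessments are conducted. Bias of this kind cannot be reliably removed in analysis. The protocol's own Discussion concedes that this type of sham may not blind fully, so an avoidable further leak is harder to defend.

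**Working it through.** **1. Sections side by side**

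| Section | Subject | Relation to the access sentence in {21b} |
|---|---|---|
| {27} | Project team blinded to the data | Direct conflict: access to primary-endpoint results is not blindness to the data |
| {16b} | Allocation concealed until conclusions are drawn | Undermined by inference: interim results do not name any patient's arm |
| {17a} | Care provider, investigator and assessor blind to allocation | Undermined by inference, as above |
| {11a} | A/B password withheld from the research group | Formally intact, but open to circumvention if results are shown by letter |

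The inference has three steps. The assessor is sent each participant's letter ({16b}). There are only two letters, and each keeps its meaning throughout. So if results were shown by letter and one letter did better, staff could guess that it is the active one, and the guess would apply to every past and future patient at once. If results were shown without letters, no allocation would be inferred, but staff would still learn whether the treatment appeared to work.

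**2. Patients without complete follow-up at each look**

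Inputs: total N = 76 (Sample size {14}); looks at 30% and 70% with 8-week follow-up complete ({21b}).

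- Look 1: 0.30 × 76 = 22.8, so 23 complete; 76 − 23 = 53 remain.
- Look 2: 0.70 × 76 = 53.2, so 53 complete and 23 remain, or 54 and 22 if rounded up.

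**3. Patients whose primary endpoint is still ahead**

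The primary outcome is the BSI at weeks 1 and 2 (Outcomes {12}), so the counts in step 2 are too wide for it. Some patients without week-8 data already have their week-2 BSI.

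Inputs: recruitment from 10 October 2022 to March 2024 (Trial status). Assumption: uniform accrual to 31 March 2024, which is 538 days, with no drop-out.

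A look taken when n patients have reached week 8 (day 56) finds further patients who have passed week 2 (day 14) but not week 8:

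(56 − 14) × 76/538 = 42 × 0.1413 = 5.9

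- Look 1 (n = 23): 23 + 5.9 = 28.9 have the week-2 BSI; 76 − 28.9 = 47.1, about 47 (62%), do not.
- Look 2 (n = 54): 54 + 5.9 = 59.9 have it; 76 − 59.9 = 16.1, about 16 (21%), do not. With n = 53 the figure is about 17.

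If recruitment ends on 1 March 2024 (508 days), the remaining numbers are 46.7 and 15.7, so the result hardly depends on the day chosen.

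**4. When the looks would fall**

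Under the same assumption (31 March end):

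- Look 1 comes 23 ÷ (76/538) + 56 = 219 days after the start, in mid-May 2023.
- Look 2 comes 54 ÷ (76/538) + 56 = 438 days after the start, in late December 2023.

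Both dates precede the end of recruitment, and both precede the article's publication on 2 January 2024. A look may therefore already have taken place; the documents do not say.

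**The case against.** The strongest reply is that {16b} and {17a} protect allocation, and an interim result reveals nobody's allocation. The A/B password stays withheld under {11a}. Section {21b} does not say in what form the team sees the results. At the first look there are only about 23 patients, 11 or 12 per arm, so a guess at the active letter from the direction of the effect could be wrong. All of this stands. A reader might infer that the access sentence flatly contradicts {16b} and {17a}; the text does not support that, and the unblinding route depends on results being shown by letter.

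Section {27} has its own ambiguity. It speaks of confidentiality, and it also gives the principal investigator the cleaned data sets. On its printed words it still cannot be squared with {21b}. Even if it were read as covering only identifiable data, {21b} would remain an open-ended permission.

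A reader might also infer that every later BSI rating is compromised because staff rate the scale. The documents do not say whether the BSI is clinician-rated or self-rated. That the people who see the results are also the BSI raters is likewise an inference. Expectation could act on either kind of rating, and only on assessments made after the first look.

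Finally, a negative may have dropped out of the sentence. If so, it still needs correcting, because the published text permits disclosure.

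**Conclusion.** The point holds as a defect of conduct and consistency. As printed, the plan releases interim results on the primary endpoint, without limit, to a team that is still recruiting, treating and collecting data. This conflicts directly with {27} and weakens {11a}, {16b} and {17a} by inference.

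The exposure is about 53 and 23 of 76 patients by incomplete 8-week follow-up. For the week-2 primary assessment it is about 47 (62%) and 16 (21%), assuming uniform accrual. These figures count patients who could be affected. They do not measure bias, whose size cannot be computed from the documents, and they do not show that any has occurred. The matter should be settled before any further interim result is released.

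**What to change.** Replace the access sentence in {21b} with wording such as:

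> Interim comparative results are seen only by the independent statistician and the DMC; the research team, TSC and sponsor receive only the recommendation to continue or stop.

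Then reconcile {21b} with {11a}, {16b}, {17a} and {27}, so that all of them state the same rule on who sees what, and until when.

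If a look has already been shared, document who saw which results, in what form (by letter or not) and when, and report it as a limitation. A comparison of patients assessed before and after that date may be shown as exploratory only. With 76 patients it would be imprecise, and it is confounded with calendar time, so it cannot rule bias out.

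The cost is one sentence in the protocol, the same rule in the DMC's terms of reference, and minor edits to the related sections. If a disclosure has occurred, add a short access record and a reported limitation. Sample size, visits and the timing of the looks do not change.
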